#### Secondary outcomes

Secondary outcomes are psychological reactions to genetic test feedback and actual behavior change as assessed by adherence to the individual weight control tips in the leaflet. Immediately after receiving genetic feedback (FA group after allocation, AO group after 8 months, see Figure 1), participants will complete a questionnaire concerning their psychological reactions using 18 items adapted from the vignette study by Meisel *et al*. [9]. One example is ‘Knowing my FTO gene test result provides me with an explanation for my body weight’ (strongly disagree to strongly agree).

#### Adherence to the weight loss tips

Adherence to the weight loss tips will be assessed by asking: ‘How often in the last month did you… (watch portion sizes, avoid second helpings, slow down your eating, avoid eating mindlessly/focus on your food, pass up extra snacks between meals, avoid sweet drinks or chose a lite drink, integrated some physical activity into your day)’*.* Response options were given on a Likert scale, ranging from ‘never’ to ‘always’*.*

#### Body composition

Follow-up anthropometric measurements will be collected at eight-month follow-up as at baseline.

#### Comprehension of the genetic test result

Immediately after receiving their genetic test feedback, participants will be asked what their genetic test result was (AA, AT, TT, I don’t know), and whether their test result puts them ‘at lower/average/higher risk for gaining weight’, also including the option ‘don’t remember’ to assess comprehension of the test result.

### Minimizing drop out

We anticipate about half the participants not returning for follow-up measures because attrition rates of this magnitude have been reported from other longitudinal studies with students for example, [39,40]. To minimize attrition, we will send several email reminders; this has been shown to increase follow-up rates [41]. We will also offer a modest incentive (£5 voucher) to everyone who fills out the follow-up questionnaire *and* returns for the final weighing session. We feel that this is justified by the time and effort participants spend taking part in the study.

### Sample size and assumptions

A power calculation conducted *a priori* using *GPower* (version 3.1; http://www.psycho.uni-duesseldorf.de/abteilungen/aap/gpower3/download-and-register)showed that a total sample size of n = 340 should suffice to detect a small effect (η = 0.25) for motivation to prevent weight gain between ‘Feedback and Advice’ and ‘Advice Only’ group with 95% power or greater at the 5% significance level, accounting for an attrition rate of 60% (based on research with other student samples). We chose the small effect size based on data from the vignette study [9] and on *FTO*s moderate effects on weight.

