### Randomization

All consenting participants will be randomized to ‘FA’ (intervention) or ‘AO’ (control) after baseline data collection is complete and records have been anonymized using serial numbers. For group allocation, we will use the randomization function in the Statistical Package for Social Sciences (SPSS 19 for Windows®; SPSS Inc., Chicago, IL, USA), which randomly assigns a set percentage of cases to a specified number of groups. Each group will consist of 400 participants, and based on population frequencies of *FTO* we expect 252 to have at least one higher-risk (A) allele and 148 to have the lower-risk (TT) genotype. Randomization will take place after data collection of each wave is complete, but before the DNA analyses are conducted. Experimenter bias is unlikely, as records are anonymous and not easily identifiable. Although neither researchers nor participants will be blind to group allocation, follow-up weights will be measured objectively and print-out records kept, which excludes inadvertent manipulation of records. Questionnaire data will be collected online, which minimizes the risk of missing data or inadvertent manipulation.

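### The stated n = 340 does not give 95% power once 60% attrition is applied correctly, and the effect it is based on is medium, not small

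*Protocol article*

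**What the plan says.** Under 'Sample size and assumptions', a G*Power calculation "showed that a total sample size of n = 340 should suffice" "to detect a small effect (η = 0.25) for motivation to prevent weight gain", "with 95% power or greater at the 5% significance level, accounting for an attrition rate of 60" per cent. The paragraph calls the effect small twice. It does not name the test or its sidedness, and it does not say whether 340 counts participants enrolled or analysed.

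Other sections bear on the same calculation:

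- 'Randomization': "Each group will consist of 400 participants". The Abstract and 'Participants' also give n = 800.
- 'Minimizing drop out': "We anticipate about half the participants not returning for follow-up measures".
- 'Primary outcome' and 'Statistical analyses': participants who have been controlling their weight for more than one month are left out of the analysis. The proportion expected is not given, and the sample-size paragraph does not mention this loss.
- 'Statistical analyses', Primary: the group comparison is by ordinal logistic regression.

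**The concern.** The number 340 is said to allow already for 60% attrition, yet the trial plans 800, and no sentence links the two. An effect of 0.25 labelled η is an analysis-of-variance quantity, and in a two-group comparison it is not small by the usual conventions.

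What is at stake is how the result on the primary hypothesis is read. A reader who accepts at least 95% power for a small effect could take a null result as good evidence against one. If the calculation is really for a medium effect, the trial could miss a small one about as often as it finds it.

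**Working it through.** **Inputs.** From the article: total 340, effect 0.25, power 95%, significance level 5%, attrition 60% ('Sample size and assumptions') or about 50% ('Minimizing drop out'), 800 planned, 1:1 allocation. Assumed: two-sided test, two-group F test with noncentrality N × f², and the usual Cohen labels (d = 0.2 small, d = 0.5 medium).

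**Conversions for two equal groups.** d = 2f, so f = 0.25 is d = 0.50. If 0.25 is η, then f = √(0.0625 / 0.9375) = 0.258, or d = 0.52. If 0.25 were d, then f = 0.125.

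**Step 1: try to reproduce 340.** The smallest N analysed for 95% power, then inflated for 60% attrition:

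| Reading of 0.25 | Analysed | N / (1 − 0.6) | N × (1 + 0.6) |
|---|---|---|---|
| f = 0.25 | 210 | 525 | 336 |
| η = 0.25 | 197 | 493 | 315 |
| d = 0.25 | 834 | 2,085 | 1,334 |

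No correctly inflated figure is 340. The nearest match is 336, from f = 0.25 with the mistaken inflation. To keep 210 when 60% are lost, one divides by the 40% retained. Multiplying by 1.6 keeps only 336 × 0.4 = 134.

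**Step 2: take 340 as enrolled.** 340 × 0.4 = 136 analysed. Power is 82.5% at f = 0.25 and 84.8% at η = 0.25.

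**Step 3: take 340 as analysed.** Power is 99.6% at f = 0.25 and 99.7% at η = 0.25, so at least 95% is literally true. But 340 is then not the number required (210 or 197 is), and it would need 340 / 0.4 = 850 enrolled, against 800 planned.

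**Step 4: the trial as planned.** 800 × 0.4 = 320 analysed, or 800 × 0.5 = 400 at 50% attrition. Power before the exclusion:

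| Effect | 320 analysed | 400 analysed |
|---|---|---|
| f = 0.25 (d = 0.50) | 99.4% | 99.9% |
| d = 0.25 | 60.6% | 70.3% |
| d = 0.20 | 43.0% | 51.4% |

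The detectable difference at 320 is d ≈ 2 × (z for two-sided 5% + z for power) / √320. This gives 2 × (1.960 + 1.645) / 17.89 = 0.40 at 95% power and 2 × (1.960 + 0.842) / 17.89 = 0.31 at 80%.

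**Step 5: the exclusion.** Its size is not in the article. If 20% to 50% of the 320 are excluded (an assumed range), 320 × 0.8 = 256 down to 320 × 0.5 = 160 remain:

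| Effect | 256 analysed | 160 analysed |
|---|---|---|
| f = 0.25 (d = 0.50) | 98% | 88% |
| d = 0.40 | 89% | 71% |
| d = 0.25 | 51% | 35% |

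**Step 6: the ordinal analysis.** A proportional-odds check (Whitehead's method) at 320 analysed and an odds ratio of 1.57, taken as the counterpart of d = 0.25, gives power of 60% to 62%, against 60.6% from the F test. Moving to the ordinal model therefore changes little.

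**The case against.** The strongest defence is that the trial does not enrol 340. It enrols 800, more than the correct 525, and at 60% attrition it has about 99% power for f = 0.25 before the exclusion. This stands: the inflation error alone does not leave the trial short for the effect that was entered. The low figures belong to d = 0.25 and d = 0.20, effects the article never specifies. They bear on the word small, not on a calculation for f or η = 0.25.

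Two stronger readings are tempting, and neither is supported. A reader might infer that 340 cannot be traced to anything, but 336 comes within about 1% of it by a recognisable slip. A reader might also infer that the power of the trial is simply wrong. That holds if 340 is the enrolled number; if 340 are analysed, or for the planned 800 before the exclusion, power for f = 0.25 exceeds 95%.

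The two attrition figures are the weaker part. 60% can be a cautious planning value beside an expectation of about half, so this calls for a clarifying sentence. The use of an F test is itself an inference, since the article names the software but no test. Finally, the Discussion hopes only for a first indication, so a firm reading of a null result is a risk, not something the authors announce.

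None of this repairs the paragraph. It still gives a total that does not deliver the stated power if read as enrolled, and a size label that does not fit.

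**Conclusion.** The sample-size statement is wrong as written, in two respects. First, 340 is not a valid enrolled total for 95% power with 60% attrition: the figure is about 525 for f = 0.25 or 493 for η = 0.25, and 340 enrolled would give about 82% to 85% power. Second, the effect is about d = 0.5, so "should suffice to detect a small effect" is a mislabel.

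The planned enrolment of 800 is adequate for that medium effect before the exclusion. It is not adequate for a small one: about 61% power at d = 0.25 and 43% at d = 0.20 with 320 analysed. After the exclusion, 95% is not assured even at f = 0.25, where power is 88% if half of the 320 are removed.

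These results assume a two-sided test, a two-group F test, Cohen's labels and, for the last figure, an excluded share that the article does not give. The origin of 340 in a mistaken inflation is likely but inferred.

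**What to change.** Rewrite the sample-size paragraph. No extra enrolment and no change to the primary analysis are needed.

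1. Name the effect metric (f, η or d), the test and its sidedness, and drop the word small.
2. Replace 340 with the correctly inflated figure (about 525 for f = 0.25) or delete it, and tie the calculation to the 800 planned.
3. Use one attrition figure in 'Minimizing drop out' and 'Sample size and assumptions', or say that 60% is a deliberately cautious allowance.
4. State the detectable effect for the ordinal primary analysis after both attrition and the exclusion of those already controlling their weight for more than one month, with the assumed excluded proportion given. The values at 320 analysed (d about 0.40 at 95% power, 0.31 at 80%) may be quoted only as the best case before that exclusion. Used as the headline, they would overstate power again.

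The cost is a text edit and a less favourable statement of power for a small effect.

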### Statistical analyses

Differences between completers and non-completers of follow-up will be assessed with chi-square tests for categorical variables and independent-samples *t*-tests for continuous variables. Participants who had been controlling their weight for more than one month will be excluded from analysis, because the intervention will not be applicable. Correct recall of the test result will be assessed with a chi-square test. Associations between genotype status and correct recall will be assessed with a one-way ANCOVA, including age, gender and body mass index (BMI) as covariates, as recall may affect subsequent reactions.

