#### Inclusion and exclusion criteria

We will include all interested first-year students between 18 and 25 years who are able to give informed consent. We chose this age range because the association between *FTO* and BMI has been found to peak in early adulthood, with less effect thereafter [25]. As *FTO* has been found to have effects in all major ethnic groups, we will not exclude participants based on ethnicity. We anticipate that a small number of individuals suffering from eating disorders may express interest in taking part, because eating disorders are relatively common in this age group [26]. However, participants have the option of declining to see weight and body composition results. If they opt to receive their body composition assessment, they will get brief, personal feedback with it. We will be careful to avoid discriminating against anyone based on their weight (high or low) because this may impair help seeking. Instead, we will offer brief, general advice on available resources to all participants, so that those who wish to find help can do so. If a participant is distressed by the result, the principal investigator, who is a clinical psychologist, will be available for intervention. Results from earlier qualitative work indicate that gene test feedback may be helpful even for individuals with a history of eating disorders, and that provision of information should be sufficient to eliminate the risk of exaggerating tendencies for disordered eating ([name] and JW, unpublished).

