### Follow-up

#### Primary outcome

The primary outcome is motivation to engage with weight gain prevention. It will be assessed using a validated measure of readiness for behavior change [36,37] adapted to relate to prevention of weight gain. Individuals will be asked: *‘*Please mark with an ‘X’ the statement out of the next four that best describes you’: ‘I am not trying to control my weight, and I have no intention of doing so in the next month’; ‘I am not trying to control my weight, but I am thinking of doing something in the next month’; ‘I started to try to control my weight within the last month’; or ‘I have been trying to control my weight for more than a month’. Responses will be used to classify individuals into one of the five stages of behavior change outlined by Prochaska and DiClemente [38]. Participants will also be asked to rate their agreement with one statement each relating to motivation to prevent weight gain, perceived ease of weight control, and the priority they are giving to weight control (ranging from ‘never’ to ‘always’*)*. The primary outcome will be measured one month after the intervention group receives their genetic test result. We chose the respective time frame, because we saw it as crucial that participants would have had sufficient time to think about their result, to ask any questions, and to implement eventual behavior change. We will exclude participants who controlled their weight for more than one month, because the intervention will not be applicable to them.

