#### Secondary

Results from all secondary analyses will be considered as exploratory. One-way ANOVAs, followed by one-way ANCOVAs will be used to examine immediate psychological reactions to genetic test feedback in the sample overall once the AO group participants have received their genetic test results. Repeated-measures ANOVAs will be used to determine change in anthropometric measures within groups over time in the sample overall. Anthropometric differences between groups will be determined using one-way ANCOVA. Age, gender and baseline BMI will be included as covariates. Changes in diet quality, eating behavior and physical activity in the sample overall will be examined with repeated-measures ANOVAs. Changes between groups will be examined using one-way ANCOVAs, including age, gender and baseline BMI as covariates. Group differences in actual behavior change (as measured by adherence to the individual tips) will be assessed with a one-way ANCOVA. In addition, we will build an additive score of the total number of tips adhered to at least ‘occasionally’ and compare this in intervention and control group with a one-way ANCOVA. Age, gender and baseline BMI will be included as covariates. Bonferroni corrections will be used for multiple comparisons in all analyses. Within the ‘Feedback and Advice’ group, *FTO* status will be dichotomized into high/average risk, with those having at least one risk allele being classified as ‘higher-risk’. Ordinal regression analyses will be used to examine effects of risk status on motivation to control weight, as well as interactions between risk status and baseline BMI. Age and gender will also be included as predictor variables in the model. Finally, we will assess predictors of motivation to control weight with a multinomial regression analysis. We will include all potential predictors, including age, gender, *FTO* status, as well as stress, eating behavior, baseline BMI, and weight satisfaction.

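### The exclusion of established weight controllers has no consistent scope; read literally, it also removes randomised participants from the recall, reaction and eight-month weight analyses

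*Protocol article*

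**What the plan says.** The protocol article states the rule twice.

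- Under Primary outcome: "We will exclude participants who controlled their weight for more than one month, because the intervention will not be applicable to them".
- In the opening paragraph of Statistical analyses, above the Primary and Secondary subheadings: "Participants who had been controlling their weight for more than one month will be excluded from analysis, because the intervention will not be applicable". The next sentence in that paragraph is "Correct recall of the test result will be assessed with a chi-square test".

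The Secondary subsection says that ANOVAs and ANCOVAs will examine "immediate psychological reactions to genetic test feedback in the sample overall once the AO group participants have received their genetic test results". It describes within-group change in anthropometric measures in similar whole-sample terms. For the between-group anthropometric ANCOVA it names no population.

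The people to be excluded can be recognised from the fourth response to the readiness item, "I have been trying to control my weight for more than a month". On timing, the article says: "The primary outcome will be measured one month after the intervention group receives their genetic test result". The Baseline questionnaire section lists no earlier version of this item. It does list a restrained-eating scale, but that is not described as recording how long someone has been controlling their weight.

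**The concern.** A rule defensible for one analysis is worded so that it reaches all of them. The only reason offered is that the intervention does not apply to people already controlling their weight. That can be argued for motivation to start. It is not a reason to set aside someone's understanding of a gene result or their emotional response to it.

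Three things are at stake. First, the three places do not tell an analyst who belongs in the recall, reaction and weight analyses, so the choice could be made after the data are seen. Second, under the literal reading, data already collected from randomised people are discarded, and the between-group weight comparison loses the protection of randomisation. Third, the abstract gives possible adverse emotional or behavioural effects as part of the background to the trial, and the secondary hypotheses predict more negative affect but no more fatalism after a higher-risk result. A reassuring finding would be weaker if established weight controllers had been left out of it.

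**Working it through.** **1. Scope.** Under Primary outcome the rule is tied to motivation. In Statistical analyses it is tied to nothing, stands above all later analyses and directly precedes recall. Nothing afterwards lifts it. The phrase in the Secondary subsection, "will be used to examine immediate psychological reactions to genetic test feedback in the sample overall", could mean everyone randomised. It more naturally means both arms pooled, because it goes on to refer to the control arm having received its results and contrasts with later analyses confined to the feedback arm. It therefore does not clearly restore the excluded people.

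**2. Does the reason fit each analysis?**

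| Analysis | Does the stated reason fit? |
|---|---|
| Motivation at one month | Arguable |
| Recall of result | No: they receive the same result and are asked the same recall question |
| Psychological reactions | No: they react to the same result |
| Weight and body fat at eight months | Weak: the secondary hypothesis concerns participants receiving feedback in general |

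**3. When is status known?** It comes from the one-month item, after randomisation and after feedback.

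- *Weight comparison.* Selection uses an answer that feedback may have changed. For example, email reminders are planned, so a student who began in response to the result and replied a little late could truthfully choose the more-than-a-month option. The retained groups are then no longer the groups as randomised.
- *Missing status.* Someone weighed at month 8 who did not answer the one-month item cannot be classified. In the completer comparison, people who skipped the item have no status, so the rule could act only on those who answered.
- *Reactions.* The feedback arm completes the reaction form right after its result, before the one-month item. The control arm completes it after about eight months, well after that item. The rule therefore filters the arms by a later answer in one and an earlier answer in the other.

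**4. Size for the weight comparison.** The article gives neither a share excluded nor a power figure for weight, so there is no stated figure to reproduce. Inputs:

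- 800 randomised, 1:1 (Randomization).
- About half lost (Minimizing drop out) or 60% lost (Sample size and assumptions), leaving 800 × 0.5 = 400 or 800 × 0.4 = 320.
- Share excluded: an assumption, 20% to 40%.
- Two-sided 5%, 80% power, unadjusted two-group *t* test. The detectable difference in SD units is close to 2 × (1.960 + 0.842) / √N. The table uses the exact noncentral *t*.

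| Excluded | N from 400 | Detectable | N from 320 | Detectable |
|---|---|---|---|---|
| 0% | 400 | 0.28 SD | 320 | 0.31 SD |
| 20% | 320 | 0.31 SD | 256 | 0.35 SD |
| 40% | 240 | 0.36 SD | 192 | 0.41 SD |

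The approximation for N = 400 is 5.603 / 20 = 0.280, and for N = 256 it is 5.603 / 16 = 0.350.

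**The case against.** The strongest reply is that the rule was probably never meant to go beyond motivation. Its placement under Primary outcome suggests this, and if the whole-sample wording means everyone randomised, nobody is lost from the reaction analysis. This stands in part: the scope is ambiguous, not explicitly universal. But an unlimited sentence in the general analysis paragraph is wrong text to leave in place, not detail deferred to an analysis plan.

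A second reply is that leaving established controllers out of the weight contrast is a legitimate choice of target population, since the intervention is presented as a nudge. That would be fair if status were fixed before randomisation. It is not.

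A third reply is that all secondary analyses are declared exploratory and that, at 20% excluded, the loss of precision is small. Both are true. The planned covariate adjustment could also make the detectable differences smaller than those tabulated. This limits the weight of the point.

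A reader might go further and infer that the rule removes the students most exposed to emotional or eating-related harm. The documents do not support that. They say "eating disorders are relatively common in this age group", but expect only a few such students to come forward. No passage links long-term weight control to vulnerability, the listed baseline measures include none that diagnoses an eating disorder, and there is no basis for saying what share of such students would be excluded.

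**Conclusion.** The point holds as an inconsistency of scope with avoidable consequences. Under the literal reading, randomised participants are dropped from the recall and reaction analyses for a reason that does not fit, and from the between-group weight comparison on the strength of an answer given after feedback.

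The inconsistency and the misfit of the reason rest on the text alone. The numerical size rests on the assumed 20% to 40% share: a rise in the detectable weight difference of about 0.03–0.04 SD at the lower end and 0.08–0.09 SD at the upper. The selection problem in the weight comparison matters more than this loss of precision, but its direction and size cannot be derived from the documents. Weaker reassurance about adverse reactions is a possibility, not something they demonstrate.

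The change should be made, but the conclusion on the primary outcome does not turn on it.

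**What to change.** In the opening paragraph of Statistical analyses, limit the exclusion to the analysis of motivation. Then state that recall, psychological reactions, weight, body fat and the comparison of completers with non-completers use every randomised participant with the relevant measurement, whatever their weight-control history. Optionally, add a descriptive table of the reaction items for those who report controlling their weight for more than a month, with no test attached.

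This costs a sentence or two of wording and needs no new data. The downside is that the weight contrast will include some people for whom the leaflet may add little, which could dilute a difference between the arms.

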#### Secondary research objectives

The secondary objectives are to assess differences in adherence to the advice and weight change from baseline to eight month follow-up in those receiving genetic test feedback and weight gain prevention advice compared with advice alone. We hypothesize that participants receiving genetic test feedback, regardless of risk status, will be more adherent to the advice and gain less weight over the study period than those receiving weight gain prevention advice alone. Within the group of participants receiving feedback and advice, we will also explore psychological reactions immediately after receiving genetic test feedback, and interactions between weight status and gene test status. We hypothesize that those receiving a higher-risk genetic test result will show higher negative affect but not higher fatalism in response to their genetic test result compared to those receiving an ‘average-risk’ genetic test result. We also predict that overweight participants receiving a ‘higher-risk’ result will value having an explanation for their weight more than normal weight participants, and that overweight participants will be more motivated to prevent further weight gain in response to a higher-risk genetic test result than those receiving an ‘average-risk’ result. All secondary objectives are exploratory, because of limited power.

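### Correct recall is a yes/no outcome but is given an ANCOVA, whose standard error is right only if recall is equal across genotypes; separately, TT carries two risk labels that one recall item treats as different answers

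*Protocol article*

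**What the plan says.** The Statistical analyses section plans two steps for recall. The first is: "Correct recall of the test result will be assessed with a chi-square test". The second is: "Associations between genotype status and correct recall will be assessed with a one-way ANCOVA", with age, gender and BMI as covariates, because recall might influence later reactions.

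The section on comprehension of the genetic test result describes two items. In the first, "participants will be asked what their genetic test result was (AA, AT, TT, I don’t know" (the fourth option is not knowing). The second asks "whether their test result puts them ‘at lower/average/higher risk for gaining weight", with a further option for not remembering. Lower and average are thus separate answers.

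The risk label for TT varies:

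- Randomization: of 400 per arm, "we expect 252 to have at least one higher-risk (A) allele and 148 to have the lower-risk (TT) genotype".
- Secondary research objectives: the higher-risk group is "compared to those receiving an ‘average-risk’ genetic test result".
- Statistical analyses, Secondary: within the feedback arm, FTO "status will be dichotomized into high/average risk", and carriers of at least one risk allele are the higher-risk group. TT is therefore average.

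**The concern.** There are two separate faults, and neither causes the other.

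**Model.** Each recall item yields correct or incorrect, and genotype is categorical. Whichever of the two is the dependent variable, there is no continuous outcome for an ANCOVA. The plan's own chi-square test, one sentence earlier, treats recall as categorical. A yes/no outcome has variance p(1 − p), so if recall differs between genotype groups their variances generally differ too. With groups of unequal size, a pooled variance then gives the wrong standard error for the difference.

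**Label.** On the risk-category item, a TT participant who answers average is right under the objectives and the analysis section, and wrong if the label under Randomization is taken as the key. Only TT participants are exposed to this. A change of key would therefore move recall in one genotype group and not the other, which is the very contrast that the recall analysis tests.

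**Working it through.** **Inputs from the protocol article.** Expected genotype split per arm: 252 A-carriers and 148 TT (Randomization). The model, covariates, items and labels are as set out above. **Assumed:** all recall rates, since the article gives none.

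**The plan's own figure.** 252 + 148 = 400, and 148/400 = 37.0% TT. This reproduces.

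**Standard error of the difference in proportion correct.** Let p1 be recall in A-carriers (n1 = 252) and p0 recall in TT (n0 = 148). Covariates are left out to show the mechanism.

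- ANCOVA (pooled): SE = √[v(1/n1 + 1/n0)], with v = [n1·p1(1 − p1) + n0·p0(1 − p0)]/(n1 + n0)
- True: SE = √[p1(1 − p1)/n1 + p0(1 − p0)/n0]
- Coverage of a nominal 95% interval = 2Φ(1.96 × ratio) − 1, where ratio = pooled SE / true SE

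Worked case, p1 = 0.95 and p0 = 0.70:

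- v = (252 × 0.0475 + 148 × 0.21)/400 = 43.05/400 = 0.1076
- Pooled SE = √(0.1076 × 0.010725) = 0.0340
- True SE = √(0.0475/252 + 0.21/148) = 0.0401
- Ratio = 0.847, coverage 90.3%

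| Recall, A-carriers v TT (assumed) | Pooled SE | True SE | Ratio | Coverage |
|---|---|---|---|---|
| 90% v 90% | 0.0311 | 0.0311 | 1.00 | 95.0% |
| 95% v 85% | 0.0288 | 0.0324 | 0.89 | 91.8% |
| 95% v 70% | 0.0340 | 0.0401 | 0.85 | 90.3% |
| 90% v 60% | 0.0395 | 0.0445 | 0.89 | 91.8% |
| 85% v 95% | 0.0324 | 0.0288 | 1.13 | 97.3% |
| 70% v 95% | 0.0401 | 0.0340 | 1.18 | 97.9% |
| 60% v 90% | 0.0445 | 0.0395 | 1.13 | 97.3% |

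The ratio depends on the 63:37 split and the recall rates, not on the total number. It therefore needs no assumption about how many participants answer.

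**Type I error.** ANCOVA on a 0/1 outcome with three covariates that affect recall and no genotype effect was simulated, with 5,000 runs per setting and four levels of recall. Rejection at the 5% level was 4.4% to 5.2% at 252 v 148. It was 4.4% to 5.0% at 101 v 59, which is 40% of each group.

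**Effect of the key on the risk-category item.** Assume that 90% of A-carriers answer correctly and that every TT participant answers either average or lower. They contribute 0.63 × 0.90 = 0.567 to overall recall.

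| TT answering average (assumed) | Overall correct, key = average | Overall correct, key = lower |
|---|---|---|
| 100% | 0.567 + 0.37 × 1.00 = 93.7% | 0.567 + 0.37 × 0 = 56.7% |
| 75% | 0.567 + 0.37 × 0.75 = 84.5% | 0.567 + 0.37 × 0.25 = 66.0% |
| 50% | 75.2% | 75.2% |

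The genotype item needs no such key: TT is the one correct answer for a TT participant.

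**The case against.** **The planned test is about valid.** The article plans a test of association, not an interval, and under no association its type I error is near 5%. This stands. A reader might infer that the error bars are wrong in general; the calculations do not support that. They are right when recall is equal, and otherwise the error is moderate and can go either way.

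**Recall as a whole is not ambiguous.** A reader might infer that recall is scored ambiguously for 37% of participants. The article does not support that. The genotype item has one correct answer for everyone, and the article does not say that correct recall means the risk-category item. The 37% is also an expectation from population frequencies, and those who respond may differ.

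**The likely key can be read from the article.** The objectives describe the result that participants receive as average-risk, and the analysis section agrees. The phrase "148 to have the lower-risk (TT) genotype" stands in a statement of expected counts, not in a scoring rule, and lower may be a deliberate wrong option. The result letter, which is not shown, settles the matter. This largely stands: the label is inconsistent, but nothing shows that a wrong key will be used or that a false genotype–recall association will follow.

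**Little depends on it.** Recall is named in no objective and is not a listed primary or secondary outcome, and no model listed under Primary or Secondary uses it. This stands and limits the weight of the point.

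None of this makes ANCOVA the matching model for a yes/no outcome, or removes the two labels.

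**Conclusion.** The point holds in a limited form. ANCOVA is mismatched to correct recall. Across assumed recall rates 25 to 30 points apart at 252 v 148, its standard error is about 15% too small to 18% too large, with coverage of about 90% to 98%. There is no distortion if recall is equal. The direction depends on which genotype group recalls better, which the article gives no means of predicting.

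The label conflict is real but confined to the risk-category item and to TT participants, an expected 37%. Its effect on that item ranges from none (TT answers split evenly) to 37 percentage points of overall recall (all TT participants give the same one of the two answers), under the assumptions shown.

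Both faults sit in a supporting analysis. The ordinal regression of the primary outcome is not affected.

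**What to change.** 1. In Statistical analyses, replace the one-way ANCOVA with logistic regression of correct recall (yes/no) on genotype, with age, gender and BMI as covariates. Use a penalised or exact version if recall is close to 100%.
2. Use one risk label for TT under Randomization, the objectives and the analysis section, matching the wording of the result letter, and score the risk-category item by that label. The genotype item needs no change.

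The cost is a few words of text. No new data, extra participants or change to the questionnaire are needed. Recruitment is reported as in progress, so both changes can be made before recall is analysed.
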